### Participant timeline {13}

Figure 1 shows the intended timeline of the participating patients, from enrollment to close-out.

**Fig. 1 Fig1:**
[figure not shown]
Overview of study procedures. POPF, postoperative pancreatic fistula, LOS, length of stay

### Sample size {14}

The sample size calculation is based on the primary endpoint: the complication rate classified according to the Clavien–Dindo classification. The study is powered to detect a reduction in overall morbidity from 50 to 35%, with 80% power and a 5% two-tailed significance level [32]. The estimate is based on previous publications [6, 8]. To achieve this, a total of 133 patients per group is required. To account for an anticipated 10% dropout and loss to follow-up rate, a total of 300 patients will be included in the study.

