## Statistical methods

### Statistical methods for primary and secondary outcomes {20a}

The statistical analysis will follow the intention-to-treat principle. Baseline characteristics will be presented as means with standard deviations or medians with interquartile ranges, depending on data distribution. The chi-square test will be used for categorical variables when the expected count is ≥ 5; otherwise, Fisher’s exact test will be applied. Logistic regression models will be used to estimate odds ratios for morbidity risk and drain use. Univariable and multivariable models will be employed to assess the impact of drain placement on outcomes.

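### 133 patients per group gives about 70% power, not the stated 80%, for 50% versus 35% at a two-sided 5% level

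*Protocol article*

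**What the plan says.** The Sample size {14} section prints every input to the calculation: "The study is powered to detect a reduction in overall morbidity from 50 to 35%, with 80% power and a 5% two-tailed significance level". From this the article concludes that "a total of 133 patients per group is required". It then adds an allowance: "To account for an anticipated 10% dropout and loss to follow-up rate", "a total of 300 patients will be included in the study".

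The section on statistical methods for primary and secondary outcomes {20a} names the test: "The chi-square test will be used for categorical variables when the expected count is ≥ 5", with Fisher's exact test otherwise. At these event rates and group sizes the chi-square test applies. The Discussion describes the trial as a superiority design. Nowhere does the article mention a one-sided test, or any other input or adjustment that would lead to 133.

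**The concern.** For two proportions of 50% and 35%, a requirement of 133 per group is too low for 80% power with a two-sided 5% test. It looks like the answer for a one-sided 5% test, which is the same as a two-sided 10% test. If so, the stated power of the primary comparison is wrong.

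The trial is meant to test whether omitting drains lowers overall morbidity in low- and intermediate-risk patients, and to inform guidelines. A non-significant result will be read against the claimed power. If readers think the trial had an 80% chance of detecting a 15-point reduction when it had about 70%, they will give a null result more weight against that benefit than it deserves.

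**Working it through.** **Inputs** (Sample size {14}): p1 = 0.50, p2 = 0.35, difference 0.15, power 80%, two-sided alpha 5%, 133 per group, 10% dropout, 300 in total. Allocation of 1:1 is inferred from the equal group sizes. The test is the chi-square test (section {20a}).

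**Constants.** z = 1.960 (two-sided 5%), 1.645 (one-sided 5%) and 0.8416 (80% power). The mean rate is 0.425. The standard deviation terms are:
- null: √(2 × 0.425 × 0.575) = √0.48875 = 0.6991
- alternative: √(0.50 × 0.50 + 0.35 × 0.65) = √0.4775 = 0.6910

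**Step 1: try to reproduce 133 from the stated inputs.** The pooled-variance formula is

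n = (z_alpha × 0.6991 + z_power × 0.6910)² / 0.15²

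At two-sided 5%: (1.3702 + 0.5816)² / 0.0225 = **169.3**, so 170 per group.

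The unpooled formula gives (1.960 + 0.8416)² × 0.4775 / 0.0225 = 166.6, so 167.

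| Method, 80% power | Two-sided 5% | One-sided 5% |
|---|---|---|
| Pooled variance | 169.3 | 133.2 |
| Unpooled variance | 166.6 | 131.2 |
| Arcsine | 169.1 | 133.2 |
| Continuity-corrected (rounded up) | 183 | 147 |

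No two-sided method comes near 133. The one-sided pooled calculation does: (1.645 × 0.6991 + 0.5816)² / 0.0225 = 133.2.

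**Step 2: power that the stated size delivers at two-sided 5%.**

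Power = Φ[(0.15 × √n − 1.960 × 0.6991) / 0.6910]

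- n = 133: (1.7299 − 1.3702) / 0.6910 = 0.5205, so power is **69.9%**.
- n = 150 (all 300 evaluable): (1.8371 − 1.3702) / 0.6910 = 0.6757, so power is **75.0%**.

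Exact enumeration of the uncorrected chi-square test gives 71.2% at 133 per group and 76.1% at 150. With Yates' correction, power at 133 is 66.8%. At a one-sided 5% level, 133 per group gives 79.9%.

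**Step 3: the effect detectable with 80% power at two-sided 5%.** With 133 per group, the no-drain rate must fall to about 33.1%, a difference of 16.9 points. With 150 per group it must fall to about 34.1%.

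**Step 4: the dropout allowance.** 2 × 133 = 266, and 266 / 0.9 = 295.6, which rounds up to 300. This step is correct, but it starts from the wrong base.

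**Step 5: the enrolment that would deliver 80%.** Unpooled: 2 × 167 = 334, and 334 / 0.9 is about 371. Pooled: 2 × 170 = 340, and 340 / 0.9 is about 378.

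**The case against.** The strongest objection concerns the cause. The one-sided explanation rests on a numerical match, and other slips fit as well. Two-sided 5% with 70% power gives 133.4 (pooled). Two-sided 5% and 80% power with 50% reduced by a third to 33.3% also gives 133.4 (unpooled). The publications behind the assumed rates, and the reference cited for the calculation, are not visible here. This stands as a caution: the one-sided origin is likely but not shown. It does not rescue the statement, because each alternative changes another printed input and leaves 133 inconsistent with the text.

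A second objection is that the error leaves the type I error rate, the test and the estimand untouched, and that recruitment is well advanced (220 of 300 included as of March 2025, per Trial status). This is true. The defect lies in the claimed power, not in the validity of the eventual result. That is a reason for a light remedy, not for leaving a false figure in place.

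Third, surgeons may place a drain in patients allocated to no drain, which would dilute the intention-to-treat contrast. If 10% did so (an assumption; the article gives no rate), the no-drain arm would average 0.9 × 35% + 0.1 × 50% = 36.5%, and power at 133 per group would be about 60%. This is a separate matter, not part of the arithmetic error, and should not be counted in its size.

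**Conclusion.** The stated sample size does not follow from the stated inputs. A two-sided 5% test of 50% versus 35% with 80% power needs 167 to 170 evaluable patients per group, which is 34 to 37 more than the 133 given. The planned trial has about 70% power with 266 evaluable patients and 75% if none of the 300 is lost. No level of attrition brings it to 80%.

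This rests only on the article's own inputs, 1:1 allocation and the chi-square test it names. It does not depend on how the slip arose. Because the power of the primary comparison is misstated, it must be corrected.

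**What to change.** Keep 300 patients and the two-sided 5% test, and correct the Sample size {14} section. Suggested wording:

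> With 266 evaluable patients (133 per group), the trial has about 70% power at a two-sided 5% significance level to detect a fall in overall morbidity from 50% to 35%, or 80% power to detect a fall from 50% to about 33%. If all 300 patients are evaluable, power for 50% versus 35% is about 75%.

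Carry the same figures into the results paper, and make the 95% confidence interval for the risk difference the main basis for interpretation, especially if the test is not significant. Do not move to a one-sided test to make 133 fit. Make the correction before the results are known.

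The cost is a change of wording and a less favourable stated power; no extra patients are needed. If the sponsor prefers to deliver the stated 80%, enrolment would have to rise to about 371 to 378 while recruitment is still open.

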### Criteria for discontinuing or modifying allocated interventions {11b}

If the operating surgeon deems a drain necessary during the procedure, the patient will be removed from the allocated group and analyzed separately, in addition to intention-to-treat and per-protocol analyses. The decision to place a drain despite the patient meeting preoperative inclusion criteria and being randomized to the no-drain group is based solely on the surgeon’s clinical judgment rather than predefined criteria.

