### Plans to promote participant retention and complete follow-up {18b}

Due to the short follow-up period (90 days), complete follow-up is anticipated without the need for specific retention measures. Since the intervention occurs as a single event during surgery, the dropout rate is expected to be low. Additionally, as the informed consent does not request permission to use previously collected data or gather additional data upon withdrawal, no specific plan exists for handling such data.

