### Methods in analysis to handle protocol non-adherence and any statistical methods to handle missing data {20c}

Patients allocated to no-drain treatment but receiving a drain will be separately analyzed in addition to those being included in the intention-to-treat analysis of that group and the group also being analyzed in a per-protocol analysis. Missing data will not be imputed.

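### The stated power makes no allowance for drains placed in the no-drain arm, although the protocol permits them and keeps those patients in the intention-to-treat comparison

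*Protocol article*

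**What the plan says.** - **Sample size {14}.** "The study is powered to detect a reduction in overall morbidity from 50 to 35" per cent, "with 80% power and a 5% two-tailed significance level". On the origin of the rates: "The estimate is based on previous publications". The result is that "a total of 133 patients per group is required", and the one inflation step is "To account for an anticipated 10% dropout and loss to follow-up rate, a total of 300 patients will be included in the study".
- **Source of the rates.** Background and rationale {6a} lists the two publications cited for the rates among large retrospective cohort studies. The Discussion says the calculation rests on nationwide registry data.
- **Criteria for discontinuing or modifying allocated interventions {11b}.** A surgeon who considers a drain necessary may place one in a patient randomized to no drain. That decision "is based solely on the surgeon’s clinical judgment rather than predefined criteria".
- **Analysis set.** Statistical methods {20a} adopts the intention-to-treat principle. The section on non-adherence {20c} says: "Patients allocated to no-drain treatment but receiving a drain will be separately analyzed in addition to those being included in the intention-to-treat analysis". A per-protocol analysis is also planned.
- **Retention {18b}.** "the dropout rate is expected to be low".
- **Concealment mechanism {16b}.** Allocation takes place in theatre once the decision to resect is made, partly so that patients with unexpected findings can be left out.

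**The concern.** Dropout and crossover reduce power in different ways. Dropout removes patients, and recruiting more replaces them. Crossover leaves the number of patients unchanged but moves the no-drain arm's event rate towards that of the drain arm, so the tested difference is smaller than the one used for sizing. The protocol has an allowance for the first, which it expects to be small, and none for the second, which it provides for explicitly.

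The 50% and 35% come from non-randomized cohort or registry data. Such sources have no randomized allocation, so their rates most naturally describe patients by the drainage they received. The primary analysis compares patients by allocation. The sample size section mentions no discount for moving from one to the other.

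The interpretation of a null result is at stake. This is a superiority trial meant to inform guidelines. If it shows no significant reduction, readers will conclude that omitting drains does not lower morbidity, when part of the result may be dilution. The planned per-protocol and separate analyses cannot settle this, because they compare groups selected by surgeons' intraoperative judgement.

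**Working it through.** **Inputs from the document:** p1 = 0.50 and p2 = 0.35; two-sided 5% level; 80% power; 133 per group; 10% dropout; 300 in total (Sample size {14}). Allocation is 1:1.

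**Input not in the document:** the crossover share c, meaning the proportion of the no-drain arm given a drain. A range of 0 to 20% is shown.

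**Step 1: the plan's own figure.** With the pooled-variance normal approximation,

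n = [z_α √(2p̄(1 − p̄)) + z_β √(p1(1 − p1) + p2(1 − p2))]² / (p1 − p2)².

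Here p̄ = 0.425, so the two roots are √0.48875 = 0.6991 and √0.4775 = 0.6910.

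- Two-sided 5%: (1.960 × 0.6991 + 0.8416 × 0.6910)² / 0.0225 = 169.3, so 170 per group. Other two-sided variants give 167 to 183.
- One-sided 5%: (1.645 × 0.6991 + 0.8416 × 0.6910)² / 0.0225 = 133.3, so 134 per group (132 unpooled).

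The stated 133 therefore fits a one-sided test and not the two-tailed test named. At 133 per group the two-sided power is Φ[(0.15√133 − 1.960 × 0.6991) / 0.6910] = Φ(0.520) = 69.9%. This is a separate problem, but it sets the starting point here. The dropout step is consistent: 266 / 0.9 = 296, against 300 planned.

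**Step 2: dilution.** Assume a crossed-over patient has the drain-arm risk of 50%. The no-drain arm rate becomes 0.35 + 0.15c, and the difference becomes 15(1 − c) points. At c = 10% this is 50% against 36.5%, or 13.5 points. Power at 133 per group is Φ[(0.135√133 − 1.960 × 0.7006) / 0.6941] = Φ(0.265) = 60.4%.

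| c | No-drain arm rate | Difference (points) | Power, 133 per group | Power, 150 per group | n per group for 80% |
|---|---|---|---|---|---|
| 0% | 35.0% | 15.0 | 69.9% | 75.0% | 170 |
| 2.5% | 35.4% | 14.6 | 67.6% | 72.8% | 179 |
| 5% | 35.75% | 14.25 | 65.3% | 70.5% | 189 |
| 10% | 36.5% | 13.5 | 60.4% | 65.7% | 211 |
| 20% | 38.0% | 12.0 | 50.5% | 55.4% | 268 |

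All powers are two-sided 5%. The 150 column is the case of no dropout at all.

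**Step 3: does the loss depend on the sidedness problem?** No.

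- At 170 per group, two-sided, power is 80.2% with no crossover, 75.9% at 5%, 71.1% at 10% and 60.7% at 20%.
- At 133 per group, one-sided, it is 79.9%, 76.1%, 72.0% and 62.9%.

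Correcting the sample size for a two-tailed test would leave the crossover loss in place.

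**The case against.** Five points can be made for the plan.

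1. **The premise is inferred.** A reader might take it as stated that 35% is the rate in an arm where nobody has a drain. The protocol does not say so, and the figures could be read as a target difference between allocated groups. This stands as a caveat. The cohort and registry origin makes the as-received reading the more natural one, but does not prove it.
2. **Crossover is limited by design.** Patients at high predicted fistula risk are excluded, and the theatre opt-out removes some likely crossovers before allocation. It would be wrong to say that surgeons may place drains freely: {11b} applies when a drain is deemed necessary. This also stands, but {11b} and {20c} still provide for drains after allocation, so crossover is limited and not removed.
3. **The size is unknown.** No rate is given, and at 2.5% crossover the loss is only about 2 points. This stands. The table is a range and not an estimate, and nothing in the document supports its upper end in particular.
4. **The direction depends on who crosses over.** A reader might infer that discretionary drains go to higher-risk patients and so dilute the difference more. That does not follow: dilution depends on what the drain does in those patients, not on their baseline risk. Purely as an illustration, suppose 10% cross over and their risk is 60% with a drain and 70% without. The no-drain arm rate then falls from 35% to 35 − 0.10 × (70 − 60) = 34%, and the difference widens to 16 points. The table holds only under the stated drain-arm-risk assumption.
5. **Supportive analyses already exist.** They do, but both condition on the surgeon's decision and so lose the protection of randomization.

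**Conclusion.** The concern holds in a limited form. The protocol foresees drains in the no-drain arm, analyses those patients as allocated, and gives a power figure with no visible allowance for them. The 10% for dropout does not fill that gap.

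Under the drain-arm-risk assumption the loss is about 2 points at 2.5% crossover, 5 points at 5%, 9 to 10 points at 10% and 19 points at 20%, all relative to 70% at 133 per group. It would be wrong to attribute the whole fall from 80% to crossover: the first 10 points come from the mismatch between 133 per group and a two-tailed test.

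The document does not show that crossover is frequent or that the trial is underpowered because of it. It shows that the stated power takes no account of it and that the sponsor can settle its size with a count. This should be addressed; how much it matters depends on that count.

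**What to change.** - **Count crossover.** Among the 220 patients reported as included in Trial status, obtain the proportion of the no-drain arm given a drain. This needs allocation and drain placement only, and no outcome data. With about 110 patients per arm (220 / 2, assuming balance), an observed 10% would carry a 95% interval of roughly 0.10 ± 1.96 × √(0.10 × 0.90 / 110) = 4% to 16%, so power should be given over that interval.
- **Restate the power in Sample size {14}** for the intention-to-treat contrast, with the diluted difference (50% against 36.5% at 10% crossover, for example) and its assumption. Do this together with the correction of the sidedness mismatch.
- **State that the 10% allowance covers missing outcomes only.**
- **Report the crossover proportion beside the primary result.**
- **Add a complier-average estimate** with allocation as the instrument, alongside the per-protocol and separate analyses. If all drain-arm patients receive a drain, it is the intention-to-treat difference divided by (1 − c): 13.5 / 0.90 = 15 points at 10% crossover. State its assumptions, chiefly that allocation affects morbidity only through drain placement and that no patient would receive the opposite of each allocation. It rescales the estimate and does not restore lost power.

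The cost is protocol wording, one count and one supportive analysis, with no extra patients. The downside is a less favourable stated power.

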### Recruitment {15}

To enhance the screening process for study enrollment, the pancreatic duct diameter is included as a standard measurement in tumor board discussions at all participating sites. Additionally, the involvement of research nurses in tumor boards will help ensure the identification of eligible participants.

## Assignment of interventions: allocation

### Sequence generation {16a}

Randomization will be conducted at each participating center by a research nurse using a computer-generated sequence with blocks of eight. Block randomization ensures balance between treatment groups and will be implemented at each site, with blocks of eight distributed accordingly. The research nurse responsible for randomization will not be involved in patient care to maintain allocation integrity. Since participating centers routinely perform either pancreatojejunostomy or pancreatogastrostomy as their standard reconstruction method, stratification for this factor is not required.

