### Concealment mechanism {16b}

Allocation concealment will be ensured using opaque, identical envelopes for all groups. Patients preoperatively enrolled in the study will be randomized prior to surgery but allocation is done in the operating theater at the time the decision to proceed with resection is made. This is done to reduce dropouts due to non-resections and to allow for an “opt out” in case of unexpected intraoperative findings.

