### Implementation {16c}

The randomization will be performed by a research nurse who will not participate in patient care, patient allocation is done in the operating room by the leading surgeon.

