## Assignment of interventions: blinding

### Who will be blinded {17a}

The DRAIN1 trial is an open-label trial.

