However, certain limitations must be considered. First, the lack of standardization in surgical indications, procedures, and postoperative treatments introduces heterogeneity. While this may improve external validity, it also increases susceptibility to bias. Second, the COVID-19 pandemic reduced the enrollment rate, which may affect results due to evolving treatment approaches for pancreatic head tumors. The superiority design of the trial could be questioned given the perceived benefits with no drain for a patient. However, when this trial was designed there was a strong drain policy in most pancreatic centers and a non-inferiority design was deemed too weak for clinically meaningful results. The final allocation of study participants in the operating room may induce a selection bias as events during surgery might prevent surgeons from enrolling certain patients. This was included in the study plan as a safety measure and reasons for not allocating patients as well as their outcomes were documented.

Another limitation is the absence of standardized early drain removal in the control group. However, this is unlikely to impact the study results significantly, as participating centers have adhered to early drain removal protocols for over a decade when no POPF signs are present. Additionally, since the trial was designed nearly a decade ago, newer predictive models for POPF have emerged. The selected model may be subject to criticism, as some may argue that other models are more relevant.

Lastly, at the time of trial initiation, minimally invasive PD was not performed in Sweden and was therefore not included in the protocol.

Despite these limitations, the study is expected to provide valuable insights into the necessity of routine drain placement in patients with low to intermediate risk for POPF. The findings may contribute to a shift in clinical practice, leading to more patients being treated without routine intraoperative drain placement.

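### One fixed block size per site, with an opt-out just before allocation in theatre, could let a fully informed surgeon foresee up to 20% of allocations

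*Protocol article*

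**What the plan says.** All references are to the Protocol article.

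- **Sequence generation {16a}:** a research nurse outside patient care randomises at each centre "using a computer-generated sequence with blocks of eight". The blocking "will be implemented at each site, with blocks of eight distributed accordingly". No other size, and no variation in size, is mentioned.
- **Who will be blinded {17a}:** "The DRAIN1 trial is an open-label trial".
- **Concealment mechanism {16b}:** "Allocation concealment will be ensured using opaque, identical envelopes for all groups". Patients are randomised before the operation, but "allocation is done in the operating theater at the time the decision to proceed with resection is made". The section gives two reasons: fewer dropouts from non-resection, and room to opt out if the operation shows something unexpected.
- **Implementation {16c}:** "patient allocation is done in the operating room by the leading surgeon".
- **Sample size {14}:** "a total of 133 patients per group is required". Equal groups imply 1:1 allocation, although no ratio is stated.
- **Discussion:** "The final allocation of study participants in the operating room may induce a selection bias". The article attributes this to events during surgery, calls theatre allocation a safety measure, and says that the reasons for not allocating patients, and their outcomes, were documented. It does not mention predictable blocks.

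**The concern.** Each feature is tolerable alone. Together they mean that the person who decides whether a patient enters the comparison may sometimes be able to work out the arm first. Opaque envelopes and an uninvolved nurse protect the list. They do not stop deduction from earlier allocations, which are visible at an open-label site.

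The surgeon may also hold prognostic information at that moment that eligibility did not use. Eligibility rests on a score built from body mass index and duct width (Eligibility criteria {10}). The Background names soft gland texture among the features carrying the highest fistula risk, and reports that 8 of the 10 patients who died in the earlier multicentre trial had a soft pancreas. If patients who look difficult were opted out more often when no drain was expected, the no-drain arm would be the lower-risk arm, which favours the trial's hypothesis. The opposite preference would push the other way. In either case the imbalance arises before allocation, so an intention-to-treat analysis of allocated patients cannot undo it.

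**Working it through.** The article gives no figure for predictability, so there is none to reproduce.

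**Inputs.** Block size 8, run per site ({16a}); 1:1 allocation, so 4 + 4 per block (implied by {14}); earlier allocations visible (open label, {17a}); 300 patients planned ({14}), 220 included as of March 2025 (Trial status).

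**Step 1: allocations certain in advance, with full knowledge of the block.** There are C(8,4) = 70 equally likely blocks. An allocation is certain once all four places of one arm are used. Counting the blocks in which this has happened before each position:

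| Position | Blocks with one arm used up | Share of 70 |
|---|---|---|
| 1–4 | 0 | 0% |
| 5 | 2 × C(4,4) = 2 | 2.9% |
| 6 | 2 × C(5,4) = 10 | 14.3% |
| 7 | 2 × C(6,4) = 30 | 42.9% |
| 8 | 2 × C(7,4) = 70 | 100% |

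The expected number per block is (2 + 10 + 30 + 70)/70 = 112/70 = 1.6, and 1.6/8 = 20.0%.

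**Step 2: best guess.** Always guessing the arm with more places left is right on average 4 + (2^8/70 − 1)/2 = 5.33 times per block, and 5.33/8 = 66.6%, against 50% for a coin toss.

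**Step 3: incomplete knowledge.** Suppose each earlier allocation is unknown to the surgeon with probability q (assumed). Certainty then requires all four allocations of the used-up arm to have been seen, so the share is 0.20 × (1 − q)^4:

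| q | Certain allocations |
|---|---|
| 0% | 20.0% |
| 5% | 16.3% |
| 10% | 13.1% |
| 20% | 8.2% |
| 30% | 4.8% |

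**Step 4: in patients.** At the ceiling, the 300 − 220 = 80 patients still to come contain 80 × 0.20 = 16 certain allocations.

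**Step 5: varying block sizes.** This was simulated with 2000 sequences of 72 allocations and an observer who knows the set of sizes and every earlier allocation:

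| Block sizes | Certain | Best guess right |
|---|---|---|
| 8 only | 20.0% | 66.6% |
| 4, 8 | 7.5% | 67.9% |
| 4, 6, 8 | 2.3% | 67.8% |
| 6, 8, 10 | 1.6% | 66.1% |

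Mixing three sizes removes most of the certainty. It hardly changes the advantage of guessing.

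**The case against.** **The 20% needs knowledge that the article does not show anyone had.** This stands. The article does not say that surgeons were told the block size or where a block begins, and publication can affect only later patients. That the surgeon personally opens the envelope is also an inference from {16c}. A reader might infer that one allocation in five was predictable in practice, or that 60 of 300 (300 × 0.20) were. The documents do not support that: it would need every block at every site to be completed and fully tracked since 2016.

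**Unopened envelopes would break the deduction.** If randomisation before surgery uses up a place even when the patient is then not resected or is opted out, the site cannot reconstruct the block. If a place is used only when the envelope is opened, the ceiling is reachable. A reader might also infer that opted-out patients are randomised and then dropped, against the intention-to-treat principle in Statistical methods {20a}. The Discussion speaks of not allocating such patients, which favours the second reading. What remains is loose wording in {16b}, not a demonstrated breach.

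**A worried surgeon has another route.** Under {11b} a drain may be placed after no-drain allocation, and {20c} keeps that patient in the intention-to-treat analysis. This weakens the incentive to opt out but does not remove the possibility.

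**The bias is already disclosed and opt-outs are documented.** This is true, and it helps detection. Documentation does not prevent the bias, and the disclosure concerns surgical events, not predictability.

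**Procedural detail may sit in the full protocol.** This is fair for the timing of envelope opening and the formal analysis set. It does not cover the fixed block size, which the article states outright.

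**Conclusion.** The point holds as a cheap improvement. The stated scheme lets a surgeon with full knowledge of a site's current block know up to 20% of allocations before deciding whether to opt the patient out. If 5–30% of earlier allocations are unknown, the share is about 16–5%. These figures rest on 1:1 allocation, a known block size and start, and places used only when envelopes are opened. For the patients still to come the ceiling is 16 allocations, fewer if recruitment has advanced since March 2025.

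The documents do not show that any opt-out was influenced by a predicted arm. They also give no basis for computing the resulting bias in the morbidity difference.

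**What to change.** 1. **Envelopes.** For the remaining allocations, replace the unused envelopes with a sequence of randomly varying block sizes, drawn from at least three sizes and not disclosed to the sites. On the figures above this cuts certain allocations to about 2%.
2. **Order of events.** Guessing stays near 66–68% accurate, so record the decision to proceed or opt out, with its time, before the envelope is opened. This does not stop anticipation. It excludes opt-outs after the arm is known and makes the pattern checkable. The opt-out itself is left as it is.
3. **Sensitivity check.** Compare the documented opt-outs by position in the block (early or late) and by the arm next due, including those among the first 220 patients.
4. **Analysis set.** State that the intention-to-treat set is all patients whose envelope was opened, and align the wording of {16b} with {20a}.

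The cost is a new set of envelopes for at most about 80 patients and one line on the theatre form. The downside is slightly less exact balance within site; a block of eight cut short at the switch can leave a site at most four apart.
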